### Study setting

2.2

This study takes place in two rural counties, Coos and Curry, on the Southern Oregon Coast as a collaboration between local community partner Bay Area First Step (BAFS) and Oregon Health & Science University (OHSU) in Portland, Oregon. These counties are highly rural, with more than 98 % and 100 % of their territory, respectively, classified as rural (Census.gov | U.S. Census Bureau Homepage, 2025). Coos County has a population density of ~39 persons/sq mi, while Curry County is even more sparsely populated at ~13 persons/sq mi (Census.gov | U.S. Census Bureau Homepage, 2025). These characteristics contribute to limited healthcare infrastructure and access in both areas.

BAFS is a peer-led community-based service organization that provides housing and peer-delivered services designed to support PWUD and their families in these rural counties. BAFS leadership and staff contributed to the design of the intervention providing input on study procedures, recruitment strategies and feasibility within the local service context. BAFS plays an active role in the community and fosters strong relationships with potential study participants. In the past 12 months, BAFS has served over 1500 individuals, the majority of whom (88 %) were between the ages of 25 and 64. Most clients identified as White (74 %) and male (59 %), although BAFS also reaches a diverse population. BAFS has prior experience implementing and recruiting participants for new service and research initiatives, supporting the feasibility of achieving the proposed sample size. BAFS peers will recruit, screen, and link eligible individuals to care. Two BAFS peers have been trained and serve as research assistants, collecting participant consent and survey data.

In Oregon, to be certified as a peer, individuals must be older than 18 years, successfully complete an Oregon Health Authority approved training program and pass a criminal history background check. Depending on the specialization, training is 40 h for Peer Support Specialists (PSS), or 80 for Peer Wellness Specialists (PWS) and includes essential skills for peer support, person-centered communication techniques, and a range of other key competencies and guiding principles. Oregon requires recertification every three years and peers must complete a minimum number of hours, depending on the certification, of continuing education.

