### Sample size and power

2.4

As part of Aim 1 and to reach enrollment goals, we plan to screen at least 220 individuals for elevated BNP levels, identifying people who use methamphetamine at risk for heart failure. This estimate reflects an initial screening target; however, the study is powered on the number of individuals who screen positive rather than the total number screened, and screening will continue as needed to enroll 122 participants with elevated BNP. We will continue screening as needed to reach our target enrollment. No prior study has reported the prevalence of positive screening (using BNP) for heart failure in community-dwelling people who use methamphetamine who are not already diagnosed with cardiomyopathy, however one prior cohort study with people who use methamphetamine presenting to the emergency department found that 63 % had abnormal BNP levels (Richards et al., 2018), which likely overestimates the prevalence in a community-dwelling population. In contrast, in the STOP-HF randomized controlled trial, approximately 40 % of community-dwelling primary care patients with cardiovascular risk factors had a BNP > 50 (Ledwidge et al., 2013), providing a more conservative reference point for BNP positivity in non-acute settings. Based on these findings, we anticipate that 122 individuals from those will have elevated BNP levels indicative of possible heart failure and meet other eligibility criteria, making them eligible for enrollment in the Aim 2 randomized controlled trial. Assuming a 10 % linkage to cardiology care in the enhanced usual care (EUC) arm, a sample size of 122 participants allows us to detect a clinically meaningful difference in linkage rates between study arms with adequate statistical power. So based on these considerations, this sample sizeallows detection of a 20 % increase in the linkage to cardiology care in the telecardiology arm (i.e., achieving a rate of 30 % at 2 months), assuming 80 % power for a two-sided test of proportions at α= 0.05. This baseline estimate is informed by linkage rates reported in symptomatic, hospitalized populations, which may differ significantly from outpatient screening populations, in whom follow-up care rates are expected to be lower.

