### Study assessments

2.6

Eligible participants identified through the screening process will complete follow-up surveys at 2 and 6 months (Fig. 1). Surveys are collected using REDCap (Table 1), in-person or by phone, including: demographics and housing; access to medical care and prescribed medications; heart failure symptom severity (adapted from the Kansas City Cardiomyopathy Questionnaire); heart failure diagnosis and cardiology treatment; drug and alcohol use patterns; addiction treatment utilization; harm reduction services; overdose history and related complications; perceived stigma; peer support services; quality of life (including a 0–10 visual analog scale); experiences with telehealth services. Participants in the intervention arm will additionally complete items assessing satisfaction with peer-delivered telecardiology support as part of feasibility and acceptability assessments (Weiner et al., 2017).

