**Fig. 1 fig0005:**
[figure not shown]
Overall trial design and procedures for the PEER-Heart study.

**Table 1 tbl0005:** Summary of Measures Included in the 2 and 6-Month Follow-Up Survey.

**Domain**	**Instrument**	**Description**	**Number of Items**	**Response Format**
**Demographics and Housing**	Study-specific	Recent homelessness, primary sleeping location	2	Dichotomized Open-ended
**Access to Medical Care and Prescribed Medications**	Study-specific	Access to primary care, barriers, site of care, transportation; prescribed medications	8	Dichotomized Checklist Multiple choice
**Heart Failure Symptom Severity**	Kansas City Cardiomyopathy Questionnaire (KCCQ-12, adapted)	Frequency and impact of HF symptoms (fatigue, swelling, shortness of breath, orthopnea)	4	Likert
**Heart Failure Diagnosis and Treatment**	Study-specific	HF diagnosis, echocardiogram, appointments, medication adherence, hospital visits	7	Dichotomized Checklist Visual analog scale
**Drug and Alcohol Use Patterns**	Study-specific, ASI-Lite	Types of substances used, frequency, route of administration, craving, alcohol use	10	Checklist # of days Sliding scale
**Addiction Treatment Utilization**	Study-specific	Inpatient/outpatient treatment, self-help groups, addiction medications, contingency management	9	Dichotomized Open-ended Checklist
**Harm Reduction Services**	Study-specific	Injection practices, equipment sharing, source of syringes and supplies	7	Multiple choice # of times Checklist
**Overdose History and Related Complications**	Study-specific	Overdose events, naloxone administration, stimulant-related physical or mental complications	5	Dichotomized Open-ended # of times
**Perceived Stigma**	Substance Use Stigma Mechanisms Scale (adapted)	Internalized and anticipated stigma related to drug use	7	Likert Dichotomized
**Peer Support Services**	Peer Support Scale (PSS-10, adapted)	Quality, respect, safety, sensitivity, and perceived benefit of peer support received	10	Dichotomized Likert
**Quality of Life (including a 0–10 visual analog scale)**	CDC HRQoL + Visual Analog Scale	Self-rated well-being, general health, days with poor physical/mental health and functional limitations	5	0–10 scale Multiple choice # of days
**Experiences with Telehealth Services**	Study-specific	Satisfaction, usability, comfort, willingness to use again	8	Dichotomized Likert

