#### Telecardiology intervention group

2.7.1

Participants will receive care remotely (via telephone visits or internet/EPIC MyChart facilitated virtual visits) with the telehealth-cardiology team. This team consists of a cardiologist and a clinical coordinator based out of the states alone urban academic medical center (OHSU). Participants randomized to the peer-assisted telehealth-cardiology intervention arm will receive referrals for local echocardiogram and lab testing, a virtual consultation with a cardiologist, and transitional care coordinated by a nurse care manager and peer. The cardiologist will initiate GDMT for those with reduced left ventricular ejection fraction, provide diuretics as needed for decongestion, and may recommend additional diagnostic testing. The telecardiology intervention will provide care for up to 3-months, then arrange referral with a local cardiovascular specialist. Follow-ups will occur at least monthly or as needed, and patients stable without heart failure will transition to primary care. Peers will facilitate the engagement of participants with tele-cardiology care intervention, and support participants in accessing labs, imaging, and telehealth resources.

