#### Enhanced usual care group

2.7.2

Participants randomized to EUC arm will receive a peer-assisted referral to a local primary care provider for the management of heart failure. Follow-up care will be based on current local practices. Like the intervention arm, peers facilitate initial engagement of participants with local treatment providers.

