#### Primary outcome: linkage to care at 2-months

2.8.1

The primary outcome is linkage to follow-up care at two months post-enrollment, defined as having successfully completed a visit with a cardiologist for evaluation of risk related to methamphetamine-associated heart failure. We hypothesize that the intervention group will experience a higher proportion of linkage to cardiology care at two months post-randomization compared to the usual care group. The sample size determination is based on detecting a meaningful difference in this outcome (detailed in the *2.4. Sample Size and Power* section).

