### Analysis

2.9

#### Aim 1

2.9.1

We assess acceptability by determining what proportion of peers can conduct the screening outreach intervention; we will assess fidelity based on which aspects of screening were completed. During audit and feedback meetings with peers, we will assess ease and barriers to implementing the screening as intended. We will descriptively examine patterns of reach and acceptability within the rural population served.

As part of the implementation evaluation of Aim 1, clinic study investigators will review positive screens and subsequent testing results (i.e., echocardiography has been performed, and whether the echocardiogram reveals structural heart disease).

#### Aim 2

2.9.2

We hypothesize that participants assigned to the intervention group will experience a higher proportion of linkage to cardiology care at 2-months (primary outcome). We will test statistical imbalance between the intervention and control groups on baseline demographic characteristics; those showing significant imbalance will be included as covariates in the primary outcome model. Linkage to cardiology care at 2-months, the primary outcome, will be analyzed with a generalized estimating equation (GEE) model with binomial family and logit link, which allows us to control correlation introduced by peer site. Missing data is imputed as not retained, and robust standard errors will be used for hypothesis tests.

Secondary outcomes will be tested using GEE models with appropriate distributions and link functions; we test hypotheses of within- and between-group changes over time (screening, 2, and 6 months), comparing the intervention to EUC. Missing secondary outcome data will be handled using multiple imputations if missing at random is a reasonable assumption, single imputation if missing not at random. Sensitivity analyses will be carried out to evaluate the impact of missing data.

Details on the sample size justification, including assumptions about baseline rates and detectable effect sizes, are provided in Section 2.4. Sample size and power.

#### Aim 3

2.9.3

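### Scoring missing primary outcomes as failures is not conservative if EUC outcomes go missing more often, because the article does not describe ascertaining the cardiologist visit in the same way in both arms

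*Protocol article*

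**What the plan says.** - **Missing-data rule (2.9.2, Aim 2).** After naming a logit GEE for linkage at 2 months, the article says: "Missing data is imputed as not retained, and robust standard errors will be used for hypothesis tests".
- **Outcome (2.8.1).** Linkage is "defined as having successfully completed a visit with a cardiologist for evaluation of risk related to methamphetamine-associated heart failure". The definition names no data source.
- **Intervention arm (2.7.1).** "Participants will receive care remotely (via telephone visits or internet/EPIC MyChart facilitated virtual visits) with the telehealth-cardiology team". The team sits at the academic centre that runs the study with the community partner. Follow-up is at least monthly, with a nurse care manager and peer support.
- **EUC arm (2.7.2).** "Participants randomized to EUC arm will receive a peer-assisted referral to a local primary care provider for the management of heart failure". Later care follows local practice, and peers help with initial engagement.
- **Follow-up data (2.6 and Table 1).** "Eligible participants identified through the screening process will complete follow-up surveys at 2 and 6 months". One survey domain covers "HF diagnosis, echocardiogram, appointments, medication adherence, hospital visits". No other source for the cardiologist visit is described.
- **Sample size (2.4).** 122 participants for 10% v 30% linkage, "assuming 80 % power for a two-sided test of proportions" at a 5% level. Loss to follow-up is not mentioned.
- **Sensitivity analyses (2.9.2).** One general sentence on missing data follows the text on secondary outcomes. It does not say whether it covers the primary outcome.

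**The concern.** Counting a missing outcome as a failure is usually defended as conservative. That defence needs the outcome to be missing at least as often in the intervention arm as in the control arm. Here the opposite is foreseeable. One arm has scheduled contact with the trial's own clinical team, and the event that counts is a visit to that team. The other arm is handed to outside providers and is reached for follow-up through a survey. An EUC participant who saw a cardiologist but cannot be reached at 2 months becomes a failure. If this happens more often in EUC, the rule turns a difference in follow-up into an apparent treatment effect on the primary outcome.

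A second, separate matter is that the sample size in 2.4 appears to assume that every outcome is observed.

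**Working it through.** **Inputs.** From the article: 122 in total, 10% and 30% linkage, two-sided 5% level, 80% power (2.4). Assumed: 1:1 allocation (61 per arm, ratio not stated); a share *m* of outcomes missing, unrelated to linkage. The article gives no value for *m*, so a range is shown. A plain two-proportion test stands in for the planned GEE, so the figures are approximate.

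**1. The article's own figure.** Pooled normal formula, n = 61 per arm:

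power = Φ[(d − 1.96·SE₀)/SE₁], with SE₀ = √(2p̄(1−p̄)/n) and SE₁ = √([p₁(1−p₁)+p₂(1−p₂)]/n).

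For 10% v 30%: SE₀ = √(0.32/61) = 0.0724, SE₁ = √(0.30/61) = 0.0701, so power = Φ[(0.20 − 0.1420)/0.0701] = Φ(0.83) = 79.6%. The stated 80% is reproduced, with complete outcomes.

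**2. Bias when there is no true effect.** With true linkage *p* in both arms and missing scored as failure, the expected false difference is p·(m_EUC − m_int). It favours the intervention whenever EUC has more missing outcomes. With full capture in the intervention arm it equals p·m_EUC.

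| True linkage, both arms | EUC missing | Apparent rates, EUC v intervention | False difference | Two-sided error (nominal 5%) |
|---|---|---|---|---|
| 10% | 20% | 8% v 10% | 2 points | 6.7% |
| 10% | 30% | 7% v 10% | 3 points | 9.0% |
| 30% | 20% | 24% v 30% | 6 points | 11.7% |
| 30% | 30% | 21% v 30% | 9 points | 21.1% |

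The error rates are exact rejection probabilities of the uncorrected chi-square test. The normal formula gives 6.7%, 9.1%, 11.5% and 20.6%. Nearly all the excess lies on the intervention's side: by the normal formula, 5.8% and 8.6% at 10% linkage, and 11.2% and 20.5% at 30%, against 2.5% nominal.

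**3. Power, as a separate question.** With true rates of 10% v 30% and the same loss *m* in both arms, the failure rule tests 10%(1−m) v 30%(1−m) at 61 per arm. A complete-case analysis tests 10% v 30% at 61(1−m) per arm.

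| Loss in each arm | Failure rule | Complete case |
|---|---|---|
| 0% | 79.6% | 79.6% |
| 10% | 74.1% | 75.2% |
| 20% | 67.8% | 70.1% |
| 30% | 60.8% | 64.1% |

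The rule itself costs about 1, 2 and 3 points. The rest of the fall is what any loss does to a sample with no allowance for it. In the setting of step 2 (loss in EUC only) but with true rates of 10% v 30%, nominal power rises to 84.2%, 88.2% and 91.5% at 10%, 20% and 30% EUC loss, because the bias adds to the difference.

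**The case against.** **The asymmetry is not written in the article.** A reader might infer that telecardiology records override a missing survey, so that the same person is a success in one arm and a failure in the other. No section says this. The outcome definition names no source, and the survey described is the same in both arms at the same times. If the survey is the only source and loss is equal, the rule is symmetric and shrinks a true effect: at 20% missing, 10% v 30% becomes 8% v 24%. The full protocol may also specify record checks. This stands against the strong reading. It does not remove the risk, because closer contact in one arm makes unequal survey loss foreseeable even with a single source.

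**There is follow-up information beyond the survey.** Section 2.9.1 has investigators review positive screens and later test results. That concerns echocardiography under Aim 1, not cardiologist visits, though it suggests that a look-up is practicable.

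**The large error rates need 30% linkage in EUC.** That is three times the article's assumption. This stands, so the 10% row is the main result and the 30% row shows how the problem grows.

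**The failure rule has merits.** People who cannot be reached may well be less likely to have seen a cardiologist, and about 6 expected EUC events (10% of 61) support arm-specific imputation poorly. This also stands: the point does not require multiple imputation as the primary method.

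**Not retained is a slip of wording.** Agreed. No retention outcome is defined, and the sentence follows directly on the linkage model.

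**Conclusion.** The point holds in a conditional form. The stated rule is not conservative if EUC outcomes are missing more often than intervention outcomes, and the design makes that foreseeable. With no true effect, full capture in the intervention arm and 20% or 30% EUC loss, the false difference is 2 or 3 points at the article's 10% linkage and 6 or 9 points at 30%. The loss rates, 1:1 allocation and missingness unrelated to linkage are assumptions. Smaller gaps between the arms give proportionally smaller false differences.

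A reader might also infer that the rule itself erodes the stated 80% power. The figures do not support that. Under EUC-only loss nominal power goes up, and under equal loss most of the fall comes from the absent attrition allowance. There is no shortfall at all if 10% and 30% were meant as rates that already count missing as failure. Section 2.4 does not say so; it takes the 10% from linkage rates in hospitalised populations.

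**What to change.** 1. Ascertain the 2-month cardiologist visit for every randomised participant from the same source in both arms, for example medical records or insurance claims, whether or not the survey is completed. Active insurance is an entry criterion (2.3), so claims are a plausible source.
2. In 2.9.2, write linked in place of retained. Missing = failure may stay as the primary rule for the few outcomes still unknown.
3. Add a named sensitivity analysis for the primary outcome in which missingness, and the assumed linkage among those missing, vary by arm.
4. In 2.4, say whether 10% and 30% already count missing outcomes as failures. If not, restate power for the expected loss: about 74% at 10% and 68% at 20% equal loss scored as failure.

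The cost is a records release and a look-up for up to 122 people, some added analysis wording, and possibly a less favourable stated power. The release is best obtained at consent, since unequal ascertainment is hard to repair once follow-up has ended.

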### Study participants

2.3

The PEER-Heart study recruits individuals who are residents of Coos and Curry Counties, Oregon—the BAFS service area. As this is a feasibility study conducted within existing community-based services, participants will be recruited without predefined targets for gender or race/ethnicity, and enrollment is expected to reflect the demographics of individuals accessing participating sites.

Individuals meet the following inclusion criteria: age 18 years or older, active health insurance, self-report of any MAU in last 30 days and regular use over the prior year, no client-reported diagnosis of heart failure, and able to communicate in English. We exclude individuals who report existing engagement in medical care for heart failure and/or are actively taking medications specifically prescribed for the treatment of heart failure. The study excludes prisoners and detained individuals.

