### Description of the PEER-Heart intervention

2.7

Individuals who screen positive and provide consent to enroll will be randomized to peer-assisted telehealth-facilitated intervention (intervention condition) or peer-assisted EUC (control condition). In both study arms, peers facilitate engagement to care.

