#### Secondary outcomes

2.8.2

Secondary outcomes include participants’ reported changes in confidence and knowledge of MAHF-associated heart failure risk, severity of heart failure symptoms, and adherence to GDMT.

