### Study incentives

2.10

Participants will receive up to $120 cash for participating in this study. Anyone who completes the screening assessments will be compensated $5. Those who screen positive and enroll in the study will be compensated $20 for the baseline survey, $30 for the 2-month survey, and $30 for the 6-month survey. Participants invited to participate in the qualitative interviews will receive an additional $40 following the interview. Cash is the preferred and most practical compensation, as few participants have access to transportation to travel to the nearest gift card vendor in this rural area.

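### Secondary analyses test between-group change from screening and state neither adjustment for the screening value nor a common screening mean; on the ordinary reading this loses precision, chiefly for symptom severity

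*Protocol article*

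**What the plan says.** Section 2.9.2 (Aim 2) of the protocol article states: "Secondary outcomes will be tested using GEE models with appropriate distributions and link functions". It then names the contrast: "we test hypotheses of within- and between-group changes over time (screening, 2, and 6 months", comparing the intervention with EUC. Section 2.8.2 lists the outcomes as "changes in confidence and knowledge of MAHF-associated heart failure risk, severity of heart failure symptoms, and adherence to GDMT".

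Screening comes before allocation. Section 2.7 says: "Individuals who screen positive and provide consent to enroll will be randomized". The screening value is therefore a pre-randomisation measurement, yet it is listed beside the two follow-ups as a level of the tested time factor.

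The only covariate rule in section 2.9.2 concerns baseline demographics and the primary model: "those showing significant imbalance will be included as covariates in the primary outcome model". Nothing adjusts a secondary outcome for its own screening value or sets the arms to a common mean at screening. The mean structure and working correlation of the secondary models are not stated.

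**The concern.** Randomisation makes the expected screening means equal in the two arms, so any observed difference at screening is chance. A model that gives each arm its own screening mean, and takes the treatment effect as the difference in change, subtracts that chance difference in full and so carries screening noise into the effect estimate. Adjusting for the screening value subtracts only the part that predicts follow-up.

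What is at stake is precision, not validity. The trial is sized on the primary outcome alone (section 2.4), and no power is given for any secondary outcome. With about 61 participants per arm, a wider interval for symptom severity makes a real difference easier to miss.

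The within-group tests raise a related issue. Section 2.5 lets people enter because they report symptoms at screening, so mean symptom scores may fall in both arms through regression to the mean. A significant within-arm change would then say little about treatment.

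**Working it through.** **Inputs.** Total randomised: 122 (section 2.4). Equal allocation, hence 61 per arm, is an assumption. Two-sided alpha is 0.05. The screening-to-follow-up correlation rho is not in the article, so a range is assumed.

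**The plan's own figure.** For 10% versus 30% with 80% power, the pooled two-proportion formula gives 62 per arm, or 124 in total; 61 per arm gives 79.6% power. The stated 122 is reproduced to within two participants. It concerns the primary outcome only and serves here just to fix the arm size.

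**Step 1: what the ordinary model estimates.** With free arm-by-time means, an identity link and all three times observed for everyone, the fitted means are the sample means. The 2-month arm-by-time term is then the difference in mean change scores. Simulated GEE fits (122 participants, three times, 300 runs per rho) agreed with the change-score difference to within 1e-15, under both exchangeable and independence working correlation.

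**Step 2: variances with equal SDs.** In units of the follow-up variance, per participant:
- change score: 2(1 − rho)
- adjusted for screening: 1 − rho²
- ratio, adjusted over change: (1 + rho)/2

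The detectable difference at 80% power is (1.960 + 0.842) × √(2/61) × √variance = 0.507 × √variance, in follow-up SDs. The power of the change contrast, at the effect for which the adjusted contrast has 80%, is Φ(2.802 × √((1+rho)/2) − 1.960). The last column is 122 × (1+rho)/2, the number of participants in an adjusted analysis that would match the change contrast on 122.

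| rho | Change variance | Adjusted variance | Ratio | Detectable, change | Detectable, adjusted | Power of change contrast | Equivalent N |
|---|---|---|---|---|---|---|---|
| 0.3 | 1.40 | 0.91 | 0.65 | 0.60 | 0.48 | 62% | 79 |
| 0.5 | 1.00 | 0.75 | 0.75 | 0.51 | 0.44 | 68% | 92 |
| 0.7 | 0.60 | 0.51 | 0.85 | 0.39 | 0.36 | 73% | 104 |
| 0.9 | 0.20 | 0.19 | 0.95 | 0.23 | 0.22 | 78% | 116 |

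Ignoring screening altogether has variance 1, so with equal SDs the change contrast is worse than that whenever rho is below 0.5.

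**Step 3: unequal SDs.** Let k be the screening SD divided by the follow-up SD. The change variance is 1 + k² − 2·rho·k and exceeds the adjusted variance by (k − rho)². At rho = 0.5 the ratio of adjusted to change variance is:
- k = 0.5: 0.75/0.75 = 1.00, no loss
- k = 0.8: 0.75/0.84 = 0.89
- k = 1.0: 0.75/1.00 = 0.75
- k = 1.2: 0.75/1.24 = 0.60

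**Step 4: where the loss comes from.** Empirical SDs of the 2-month contrast in the same simulations (equal SDs):

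| Model | rho 0.3 | rho 0.5 | rho 0.7 |
|---|---|---|---|
| Free screening means (change score) | 0.230 | 0.190 | 0.137 |
| Adjusted for the screening value | 0.185 | 0.162 | 0.126 |
| Common screening mean, exchangeable | 0.185 | 0.161 | 0.126 |
| Common screening mean, independence | 0.189 | 0.180 | 0.175 |

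Keeping screening as an outcome row costs nothing if the arms share a screening mean and the working correlation is not independence. With independence, screening contributes nothing to the contrast, and at rho = 0.7 the result is worse than the change score.

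**The case against.** The strongest objection is that this is detail for a statistical analysis plan. The source is a condensed article, and the sentence in section 2.9.2 fits both the efficient and the inefficient model. That stands in part: the mean structure is inferred, not quoted. But the article does name the contrast and its time levels, and a free arm-by-time model is the ordinary reading. The point is therefore an improvement to a stated method, not a complaint about silence.

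A reader might infer more than the document supports:

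- **That listing screening as an outcome time causes the loss.** It does not. The loss needs arm-specific screening means, and the text does not exclude a common mean.
- **That the secondary results would be biased.** They would not; under randomisation the change contrast is unbiased.
- **That all secondary outcomes are affected.** Section 2.3 excludes people "actively taking medications specifically prescribed for the treatment of heart failure", so GDMT adherence has no informative screening value. Table 1 names no instrument for knowledge or confidence, so the article does not show whether they qualify. That leaves chiefly "severity of heart failure symptoms".
- **That a matching baseline is known to exist.** Section 2.5 describes a symptom questionnaire at screening, and section 2.10 pays (in dollars) "20 for the baseline survey". Table 1 lists the adapted KCCQ-12 items only for the 2- and 6-month surveys. No section confirms the same items before randomisation, although the planned change from screening itself needs such a value.
- **That the gain is fixed and free for every outcome.** It shrinks to 5% of the variance at rho = 0.9 and can vanish when k = rho. With a logit link, covariate adjustment also turns a marginal odds ratio into a conditional one.

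**Conclusion.** The concern holds as a moderate, avoidable loss of precision on the ordinary reading of section 2.9.2. With equal SDs, an adjusted contrast would have 65% to 95% of the variance of the change contrast for rho from 0.3 to 0.9. Where the adjusted contrast has 80% power, the change contrast has 62% to 78%.

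These sizes rest on free arm-by-time means, an identity link, complete data, equal allocation, equal SDs and an assumed rho; correlation by peer site is ignored. They apply to continuous or score outcomes with a pre-randomisation value on the same items, chiefly symptom severity. The change is worth making, but nothing in the plan is invalid without it.

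**What to change.** Add one or two sentences to section 2.9.2 or the statistical analysis plan, for each continuous or score secondary outcome with a pre-randomisation value on the same items:

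- Define the treatment effect as the between-arm difference at 2 months and at 6 months.
- Estimate it in one of two ways. Either fit the GEE to the two follow-ups with arm, time, arm-by-time, the pre-randomisation value and its interaction with time; or keep three time points with a common screening mean across arms and a working correlation other than independence.
- Report within-arm change descriptively.
- If an outcome uses a logit link, say whether the marginal or the conditional odds ratio is intended.

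Confirm first that the symptom items at screening or at the baseline survey match those at follow-up, and that the survey precedes randomisation. If they do, no extra data are needed and the cost is the added text. If they do not, the planned change from screening is itself undefined for that outcome.
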